## 9.5 Secondary Analyses

### 9.5.1 Main Trial Analyses

**All secondary parameters** will be analyzed for the FAS.

BSID-III cognitive scale at the age of 1 year will be analysed similar to the primary endpoint. In addition, the BSID-III cognitive scale and important subscales will be analysed descriptively by group and time point using standard descriptive measures for continuous variables. The VABS total scales, important VABS subscales, ADOS total scales, and important ADOS subscales will be analysed descriptively by group and time point using standard descriptive measures for continuous variables, as well. In addition, for cognitive impairment and autism spectrum disorders at 1 and 2 years of age, 95% CIs will be calculated by treatment group in addition to the relative frequencies using the method of Wilson. The M-CHAT-R/F and TAND will be analysed descriptively by group and time point using absolute and relative frequencies.

The MRI characteristics (as defined in Section 6.8) will be analysed by group and time point, i.e. randomization (last image before randomization) and at 2 years of age  $\pm$  6 months.

Seizure characteristics, EEG characteristics, abdominal sonography characteristics, ECG and echocardiography characteristics (as defined in Section 6.8) will be analysed by treatment group and time point (if applicable).

All **safety parameters** will be analyzed for the SAF. Only treatment emergent-event adverse events will be analysed. Frequencies (number of adverse events & number and percentage of patients with at least one adverse event) will be tabulated according to system organ class and preferred term. One table each will be created showing: all adverse events, all serious adverse events, all adverse events of special interest, all non-serious adverse events, all adverse events leading to death, all adverse events related to the treatment (treated group only), all adverse events by severity. In addition, adverse events and special situations will be analysed by categories defined in the eCRF (number of events & number and percentage of patients with at least one event).

For laboratory values and vital signs, the analyses will be conducted by visit and shift tables comparing all values by visit to the relevant baseline value will be displayed additionally.

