### 2.2 Secondary Objectives and Endpoints

#### 2.2.1 Main Trial

The secondary objectives are adapted to the purpose of this study from the EPISTOP trial, a phase IIb study evaluating the impact of early versus late preventive treatment with vigabatrin on epilepsy in infants with TSC at 2 years of age [14] and will be compared between intervention and control groups:

1. Neuropsychologic outcome at 12 months of age assessed by rater blinded neuropsychologic testing using the cognitive scale on the BSID-III in both groups. Cognitive impairment will be defined as BSID-III cognitive scale score <70 similar to the EPISTOP trial [14].
2. Adaptive behaviour assessed by the Vineland Adaptive Behaviour Scales (VABS-3; digital) at the age of 12 months and 24 months.
3. Evidence for autism spectrum disorder measured at 12 months and 24 months of age by the Autism Diagnostic Observation Schedule (ADOS-2). Suspicion of autism spectrum disorder will be defined as ADOS > 12, similar to the EPISTOP trial [14].
4. Evidence for autism spectrum disorder measured by the Modified Checklist for Autism in Toddlers revised (M-CHAT-R/F).
5. TSC-associated Neuropsychiatric Disorders (TAND) severity assessed by the TAND-L Checklist (German version) at 12 and 24 months.
6. Assessment of seizure frequency and the occurrence/severity of Infantile Spasm measured by seizure diaries, caregiver questionnaires and EEG recordings.
7. Reduction of number and size of cardiac rhabdomyoma and arrhythmia (if present).
8. Reduction of cerebral tumor number and size on cMRI (if present).
9. Adverse events (AE), serious adverse events (SAE) and Adverse Events of Special Interest (AESI), assessed by the *Common Terminology Criteria of Adverse Events (CTCAE, Version 5.0)*.
10. Assessment of laboratory data and vital signs.
11. Assessment of EEG recordings for the occurrence of hypsarrhythmia and epileptiform discharges.
12. Renal changes in abdominal sonography: Volume and size of angiomyolipomas (if present), kidney size, renal pelvis dilation, echogenicity.

|                                                                    |                                              |                                |
|--------------------------------------------------------------------|----------------------------------------------|--------------------------------|

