### 9.4 Primary Analysis

As **primary analysis**, the BSID-III cognitive scale of 2 years will be analysed using a two-sided Mann-Whitney-U-test ( $\alpha=0.05$ ) stratified by age groups (0-<2 and 2-<4 months of age) comparing the treatment versus the control group. The Mann-Whitney-U-test is used instead of the t-test because there are hints that the values could be not normally distributed in this

|                                                                    |                                              |                                |
|--------------------------------------------------------------------|----------------------------------------------|--------------------------------|
| Clinical Trial Code: PROTECT
EU trial number: 2022-502332-39-00 | Trial Protocol
(Version 06; (01.10.2024)) | Page 92 of 110
CONFIDENTIAL |
|--------------------------------------------------------------------|----------------------------------------------|--------------------------------|

population. All patients randomized will be evaluated following the treatment policy strategy (ICH E9 R1).

Missing values of patients (including missing values due to early termination of the study) without a BSID-III cognitive scale at the age of 2 years will be replaced

- a) with randomly selected values of patients in the control group (single imputation) if the 1-year value is not available
- b) with data of the control patients using a linear regression model with the 1-year value as independent variable and the 2-year value as the dependent variable (single imputation) if the 1-year value is available

Values of the control group will be used in order to achieve a conservative estimate. No fixed value is used for single imputation (e.g. the median) to reduce the risk to underestimate the variance. The seed to select values randomly is 4421360.

Additionally, the median of the BSID-III cognitive scale and the corresponding 95% CI will be displayed by group.

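### Section 2.2.1 promises arm comparisons, but 9.5.1 fixes per-arm summaries for the neurodevelopmental outcomes other than the BSID-III score, and 9.4 gives the primary test no between-arm estimate with an interval

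*Protocol*

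**What the plan says.** Protocol 2.2.1 lists twelve secondary endpoints and says they "will be compared between intervention and control groups". Section 9.5.1 then sets out their analysis:

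- **BSID-III cognitive score at 1 year (item 1):** handled like the primary endpoint, so the arms are compared.
- **Cognitive impairment and autism spectrum disorder at 1 and 2 years (binary cuts within items 1 and 3):** "95% CIs will be calculated by treatment group in addition to the relative frequencies using the method of Wilson".
- **VABS and ADOS scores (items 2 and 3):** summaries only; for example, "important ADOS subscales will be analysed descriptively by group and time point using standard descriptive measures for continuous variables".
- **M-CHAT-R/F and TAND (items 4 and 5):** "The M-CHAT-R/F and TAND will be analysed descriptively by group and time point using absolute and relative frequencies".
- **Seizures, cardiac findings, MRI, EEG and renal sonography (items 6, 7, 8, 11 and 12):** no method is named. For MRI, "The MRI characteristics (as defined in Section 6.8) will be analysed by group and time point".
- **Safety, laboratory values and vital signs (items 9 and 10):** tabulated.

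For the primary endpoint, 9.4 specifies a two-sided Mann-Whitney test stratified by age group. Beyond the p-value it adds that "the median of the BSID-III cognitive scale and the corresponding 95% CI will be displayed by group". Section 9.9 refers to an observed difference in medians above 5 and calls a point estimate of 5 encouraging. Section 9.7 adds a linear mixed model with multiple imputation as a sensitivity analysis.

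**The concern.** Section 2.2.1 announces a comparison, and 9.5.1 replaces it with description of each arm. For the two binary outcomes this goes beyond leaving detail to the SAP: the protocol names a method, Wilson, and a target, each arm on its own. An SAP that follows this text would report no difference, ratio or interval between arms for cognitive impairment, autism, VABS, ADOS, M-CHAT-R/F or TAND.

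The primary endpoint has a related gap. The test yields a p-value. The difference in medians can be obtained by subtraction, but 9.4 gives it no interval. The only between-arm estimate available elsewhere comes from the 9.7 model, which works on means and imputes differently.

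At stake is how the results can be read. A reader shown two one-arm intervals may look for overlap, which is much stricter than a 5% comparison, and could dismiss a difference that the data support.

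**Working it through.** **Inputs.** 30 per arm (4.1, 9.9); cut-off 70 (9.2); example scores of 75 and 90 and SDs of 15, 20 and 25 (9.9, Table 8); alpha 0.05 two-sided (9.4). The rates 50% and 33% come from the earlier preventive vigabatrin trial cited in 1.2. Table 8 uses normality, and so does this check.

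**The plan's own figures.** Power of the Mann-Whitney test without missing values, using the normal formula with n multiplied by 3/pi and then 20,000 simulated unstratified tests:

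| Difference, SD | Table 8 | Formula | Simulation |
|---|---|---|---|
| 15, 15 | >95% | 96.6% | 96.1% |
| 15, 20 | >80% | 81.0% | 79.4% |
| 15, 25 | >62% | 62.2% | 60.2% |
| 11.5, 15 | >80% | 82.7% | 81.3% |

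Table 8 reproduces to within 2 points and is not in dispute.

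**Coverage of the twelve secondary items.** One has a stated between-arm analysis (the 1-year score in item 1). Four are fixed as description by arm (items 2 to 5). Five have no method stated (items 6, 7, 8, 11 and 12). Two are safety items (9 and 10). 1 + 4 + 5 + 2 = 12.

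**What the one-arm intervals miss.** With proportions p1 and p2, Wilson limits (l1, u1) and (l2, u2), and d = p1 − p2, the Newcombe interval is

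lower = d − √[(p1 − l1)² + (u2 − p2)²]; upper = d + √[(u1 − p1)² + (p2 − l2)²].

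Example: 14/30 against 5/30. The Wilson intervals are 30.2–63.9% and 7.3–33.6%, which overlap. d = 0.467 − 0.167 = 0.300.

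- Lower: 0.300 − √[(0.467 − 0.302)² + (0.336 − 0.167)²] = 0.064
- Upper: 0.300 + √[(0.639 − 0.467)² + (0.167 − 0.073)²] = 0.496

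The difference is 30.0 points with a 95% interval of 6.4 to 49.6, and the Fisher test gives p = 0.025. The overlapping one-arm intervals do not show this.

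**How often it matters.** Impairment rates follow from P(score < 70) = Φ((70 − mean)/SD). At SD 15, Φ(−0.333) = 36.9% and Φ(−1.333) = 9.1%. Exact binomial enumeration with 30 per arm gives:

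| Scenario | Rates | Newcombe interval excludes 0 | Wilson intervals separate |
|---|---|---|---|
| 75 vs 90, SD 15 | 36.9% vs 9.1% | 75.1% | 42.4% |
| 75 vs 90, SD 20 | 40.1% vs 15.9% | 56.2% | 24.5% |
| 75 vs 90, SD 25 | 42.1% vs 21.2% | 41.0% | 14.5% |
| Rates cited in 1.2 | 50% vs 33% | 26.6% | 7.6% |
| No effect | 40% vs 40% | 4.9% | 0.6% |

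**Primary endpoint.** In 6,000 simulated trials with a difference of 15, the Mann-Whitney test was significant while the two per-arm median intervals overlapped in about 40%, 50% and 45% of all trials at SD 15, 20 and 25. The protocol does not say how the median interval is formed; order-statistic limits (ranks 10 and 21, 95.7% coverage) are assumed.

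**The case against.** The strongest reply is that 2.2.1 names no inferential method, and tables by randomised arm are one way to compare. With 60 infants, twelve secondary items and no multiplicity scheme, confining tests to the BSID-III score is a defensible phase IIb choice. Section 9.3 also lets the SAP add analyses. This stands as an argument against more significance tests. It does not explain why two binary outcomes get an interval for each arm but none for the difference, and 9.3 permits an addition without requiring one.

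Four stronger readings are tempting, and the documents do not support them.

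- *All secondary effects must be read from overlapping intervals.* Wilson intervals are specified for two binary outcomes only. VABS, ADOS, M-CHAT-R/F and TAND have no stated interval.
- *A real benefit on cognition would go unproven.* Cognitive impairment is a cut of the BSID-III score, and that score is tested between arms at 12 and 24 months. At SD 15 the test of the score has stated power above 95%, against 75% for the binary difference.
- *The plan decides by overlap.* No section says so. The rates above measure a possible misreading. For the binary outcomes a reader could rebuild an unstratified Newcombe interval from the reported counts, though not an age-stratified one without stratum counts.
- *Imaging, EEG, seizure and cardiac contrasts are ruled out.* They are unstated, and the SAP may supply them. By-arm tables are usual for safety.

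On the primary endpoint, 9.9 speaks of a point estimate and sets no criterion on an interval. The Hodges-Lehmann shift is also a different quantity from the difference in medians used there.

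**Conclusion.** The point holds in limited form. Section 2.2.1 and 9.5.1 disagree for cognitive impairment, autism, VABS, ADOS, M-CHAT-R/F and TAND, and 9.4 leaves the primary test without a between-arm estimate and interval. The validity and power of the primary test are not in question.

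The size is illustrative: 75% against 42% at SD 15, 56% against 24.5% at SD 20, 41% against 14.5% at SD 25, and about 5% against 0.6% with no effect. These figures assume normal scores (9.4 itself doubts normality), 30 complete cases per arm, no age stratification and no control-based imputation. With 10% missing values, Table 8 reduces the difference from 15 to about 13.5, so the rates would change. At 50% against 33%, even the difference interval excludes zero in only about 27% of trials. The gain is therefore an honest statement of the effect and its uncertainty, more than extra positive findings.

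**What to change.** In 9.5.1, keep the per-arm summaries and add, labelled exploratory:

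- for cognitive impairment and autism at 1 and 2 years, the between-arm risk difference with a 95% Newcombe interval, plus an age-stratified version built from stratum-level limits where counts allow;
- for VABS and ADOS, a between-arm location difference with a 95% interval.

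In 9.4, add the age-stratified Hodges-Lehmann shift with a 95% interval as the estimate matching the primary test. Because 9.9 refers to the difference in medians, report that difference with a 95% interval as well.

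Safety tables can stay by arm. Contrasts for imaging, EEG, seizures and cardiac findings can be left to the SAP. If only description is intended for any of the remaining endpoints, such as M-CHAT-R/F and TAND, reword 2.2.1 to say so.

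The cost is a few sentences and a few lines of SAS code, with no extra patients or data. Under 9.3 the secondary changes can go into the SAP alone. The addition to 9.4 leaves the test unchanged, but 9.3 requires an amendment for changes to the primary analysis, so it is best carried in the next one. The downside is a few more exploratory intervals to report.

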group, blood tests are conducted more frequently to monitor the levels of the study medication and ensure optimal dosing and identify possible safety-relevant parameters. This may cause discomfort or pain and rare cases of bruising, local irritation, inflammation or bleeding during blood sampling. In very rare cases, injury to a superficial nerve may occur, causing superficial sensory disturbances. No placebo will be administered in the control group. This will minimize the number of laboratory examinations at screening, 6 months, 12 months, and 24 months of age to only those required to control for laboratory abnormalities unrelated to the study intervention. The study medication carries the risk of potential side effects and may cause additional discomfort when administered twice daily, which was however shown to reduce total doses as opposed to a once daily regimen (detailed below). At 12 months and 24 months of life, detailed neuropsychological evaluations will be conducted in an outpatient setting to assess the child's developmental status and behavior. These evaluations may take several hours. In addition, caregivers are asked to answer several questionnaires about the developmental status and behavior of their children, which might take up to 90 minutes.

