Qualified study personnel with at least several years of experience in pediatric care and specific knowledge of TSC and the aforementioned measurements and interventions (such as blood sampling in neonates) will minimize emotional and physical pain. Blood samples for the study are taken at the same time as those required for usual clinical care. In consultation with caregivers, the use of anesthetic plasters to minimize pain is encouraged. Emphasis is placed on communicating with parents so they are informed about the procedures. Separation of infants from parents or familiar individuals is avoided whenever possible. Facilities are designed to be child-friendly, providing a comfortable environment with appropriate furniture and toys, while avoiding cold, light, and noise. Blood collection is carefully managed, with the maximum amount based on age and weight to ensure safety. The research-related blood loss (including waste) does not exceed 3% of the total blood volume over a period of four weeks and should not exceed 1% at any time. In the group receiving the study medication (treatment group), apart from general blood tests, regular determinations of the study medication's concentration and safety-related blood parameters are collected and analyzed to control the dosage of the study medication. The number of tests and assessments is minimized whenever possible. A single blood sample (SOC and PK sampling) comprises approximately 5-10 ml. Throughout the entire study period of 21-24 months, these measurements are conducted 13 times in the group receiving the study medication, totaling approximately 65-130 ml during the study. By not including a placebo group, the number of blood collections is reduced in the comparison group. Throughout the entire study period of 21-24 months, these measurements are conducted 4 times in the group not receiving the study medication, totaling 20-40 ml during the study.

Age-appropriate formulas are used for calculating the glomerular filtration rate (GFR), and laboratory reference ranges are adjusted to the pediatric age groups. The chosen initial dose is scientifically justified within the protocol, utilizing a pharmacokinetic/pharmacodynamic model for age-adjusted dosing. [37]

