## 6.5 Treatment Visits

During the treatment phase of the study there will be visits at week 2 (V2) to months 24 (V12). If applicable, assessment of seizure diaries, the use of anti-seizure medications, adverse events to the study medication and concomitant medications will be done. Furthermore, assessment of anthropometric data, vital signs and physical/neurologic exams will be performed. Laboratory examinations during every study visit include hematology, chemistry, lipids, urinalysis, and pharmacokinetic testing if randomized to the treatment group. In the control group laboratory examinations will be reduced to a minimum at weeks 0 (V1), 6 months (V6), 12 months (V8), 24 months (V12) in order to control for laboratory abnormalities related to TSC. Refusal of participating in laboratory examinations in the control group will not lead to exclusion from the study. Dosing adjustment to the study medication (sirolimus) will be based on pre-dose PK blood sample concentrations (collection of 1-2 ml blood). Sirolimus will be dosed to attain target  $C_{min}$  ranges of 5-10 ng/ml. Additional pre-dose PK blood samples should be collected two weeks after any sirolimus dose adjustment. The high frequency of visits during the beginning of the core phase is essential to ensure that titration is being performed effectively and to ensure good compliance.

Additional sirolimus PK sampling: In addition to the time points described above, pre-dose blood samples for determination of sirolimus concentrations should be collected **one** week after the following events:

- Reduction in the dose of a CYP3A4/PgP inducer/inhibitor
- Starting, or changing the dose of, a CYP3A4/PgP inducer/inhibitor

Antiepileptic drug PK sampling: Sirolimus is metabolized by the CYP3A4 pathway in the liver. Many of the concomitantly administered ASMs are also metabolized by CYP3A4, which results in a potential for drug-drug interactions. Therefore, levels of the ASMs listed below (considered to be CYP3A4 substrates and /or inducers) will be measured to investigate the effect of sirolimus on the ASM level.

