## 8. Adverse Events

### 8.1 Definitions

#### 8.1.1 Adverse event

According to GCP, an adverse event (AE) is defined as follows: Any unexpected medical occurrence in a subject to whom a medicinal product is administered and which does not necessarily have a causal relationship with this treatment. An AE can therefore be any unfavorable and unintended sign (including an abnormal laboratory finding), symptom, or disease temporally associated with the use of an investigational medicinal product (IMP), whether or not related to the IMP.

An AE may be:

- New symptoms/medical conditions
- New diagnosis
- Changes of laboratory parameters which are considered as clinically significant
- Occurrence of new pathological and clinically relevant findings
- Aggregation of pre-existing symptoms in physical and neurological examinations, vital signs, ECGs, clinical chemistry, haematology etc.

The criteria that should be considered when determining whether an abnormal test finding should be reported as adverse event are as follows:

1. Test result is associated with accompanying symptoms, and/or
2. Test result requires diagnostic testing or medical/surgical intervention, and/or
3. Test result leads to a change in clinical trial dosing outside the protocol-stipulated dose adjustments, or discontinuation from the clinical trial, significant additional concomitant drug treatment, or other therapy, and/or
4. Test result is considered clinically relevant at the discretion of the investigator or sponsor
5. Intercurrent diseases and accidents
6. Worsening of medical conditions/ diseases existing before clinical trial start
7. Recurrence of disease
8. Increase of frequency or intensity of episodic diseases.

A pre-existing disease or symptom will not be considered an adverse event unless there will be an unexpected change in its intensity, frequency or quality. This change will be documented by an investigator (see also above).

Surgical procedures themselves are not AEs; they are therapeutic measures for conditions that require surgery. The condition for which the surgery is required may be an AE. Planned surgical measures permitted by the clinical trial protocol and the condition(s) leading to these measures are not AEs, if the condition leading to the measure was present prior to inclusion into the clinical trial.

In the latter case the condition should be reported as medical history.

AEs are classified as "non-serious" or "serious".

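### Crude AE tables will show more laboratory AEs under sirolimus even with no drug effect, because blood counts and chemistry are scheduled up to 12 times against at most 3 in controls

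*Protocol*

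**What the plan says.** **Sampling differs by arm on purpose.** Section 1.3.1 says that in the treatment group "blood tests are conducted more frequently to monitor the levels of the study medication", and Section 6.5 says "In the control group laboratory examinations will be reduced to a minimum": week 0, then 6, 12 and 24 months. Section 1.3.4, under the measures to reduce distress and pain, gives the totals: "these measurements are conducted 13 times in the group receiving the study medication" and "these measurements are conducted 4 times in the group not receiving the study medication, totaling 20-40 ml during the study". Section 6.5 adds: "Refusal of participating in laboratory examinations in the control group will not lead to exclusion from the study". Three post-screening panels is therefore a ceiling for controls.

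**Laboratory findings become AEs.** Section 8.1.1 lists among possible AEs "Changes of laboratory parameters which are considered as clinically significant". Section 6.8 likewise has pathological, clinically relevant laboratory results documented as AEs.

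**The AE analysis is stated in definite terms.** Section 9.5.1 prescribes event counts and the "number and percentage of patients with at least one adverse event) will be tabulated according to system organ class and preferred term", with separate tables by seriousness, special interest, relatedness and severity. None is limited to visits that both arms share, split by how the event came to light, or accompanied by the number of assessments. For laboratory values, the same section plans summaries by visit and shift tables against baseline.

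**The concern.** A child counts in an at-least-one-event table if the event is found once. More scheduled looks mean more findings, so the percentage depends on the sampling schedule as well as on the drug. Sections 1.3.1 and 3.1 say that controls are sampled to account for abnormalities that have nothing to do with the intervention. The AE tables do not use that sampling on equal terms.

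This matters because AEs are secondary endpoint 9, and most of the effects listed in Table 2 (from a retrospective series of treated infants) are laboratory findings, for example anaemia in 11/12 and neutropenia in 5/12 at 0 to 6 months. The rows most exposed to unequal looking are thus among those on which the safety profile will be read.

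**Working it through.** **1. Reproduce the plan's own figure.** Counting the haematology and chemistry cells in Table 1:
- Sirolimus: screening + V2 to V13 = 1 + 12 = 13.
- Control: screening + V6, V8, V12 = 1 + 3 = 4.
- Volume at 5-10 ml per sample: 13 × 5-10 = 65-130 ml; 4 × 5-10 = 20-40 ml.

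All four agree with Section 1.3.4. Post-screening panels are therefore 12 versus 3. The Table 1 footnotes allow V4 and V5 to be omitted under stated conditions, which gives 10 versus 3. Lipids and urinalysis in Table 1 are 5 (V3, V6, V8, V10, V12) versus 3 (V6, V8, V12).

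**2. At least one finding with no drug effect.** Let p be the chance that a panel yields a reportable new abnormality, the same in both arms and independent between panels. The Protocol gives no p, so p and the independence are assumptions. The share with at least one finding in k panels is 1 − (1 − p)^k.

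| p | 12 panels | 10 panels | 3 panels | ratio 12:3 | ratio 10:3 |
|---|---|---|---|---|---|
| 2% | 21.5% | 18.3% | 5.9% | 3.7 | 3.1 |
| 5% | 46.0% | 40.1% | 14.3% | 3.2 | 2.8 |
| 10% | 71.8% | 65.1% | 27.1% | 2.6 | 2.4 |

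At p = 5% and 30 children per arm, that is 30 × 0.460 = 13.8 versus 30 × 0.143 = 4.3 children.

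**3. Lipids and urinalysis (5 versus 3).** At p = 5%: 1 − 0.95^5 = 22.6% versus 14.3%, ratio 1.6.

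**4. Dependence on duration.** Independence fits short abnormalities best. As a check, one episode was given a random onset between day 60 and day 730 of age (a span of 670 days) and a fixed duration. Controls were sampled on days 183, 365 and 730. The sirolimus arm was sampled on 11 days: 74, 88, 102, 183, 274, 365, 456, 548, 639, 730 and 760 (V5 omitted).

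| Duration | Found, sirolimus | Found, control | ratio |
|---|---|---|---|
| 14 days | 20.8% | 6.3% | 3.3 |
| 30 days | 37.7% | 13.3% | 2.8 |
| 90 days | 99.0% | 40.2% | 2.5 |
| 180 days | 100% | 72.1% | 1.4 |
| 365 days | 100% | 100% | 1.0 |

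The control column can be checked by hand. At 14 days it is 3 × 14 / 670 = 6.3%. At 180 days the catching windows are 123, 180 and 180 days, so 483 / 670 = 72.1%.

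**5. Common visits only.** With V6, V8 and V12 in both arms, k = 3 on each side. At p = 5% the shares are 14.3% and 14.3%, ratio 1.0.

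**The case against.** The best defence is that Section 9.5.1 already plans laboratory values by visit with shift tables. At V6, V8 and V12 these compare the arms on equal sampling. That stands for laboratory values: the control sampling is not wasted. It does not alter the AE tables, which report a different quantity.

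A second defence is that Section 9.3 lets the SAP add analyses, and that AE start and end dates are recorded, so a common-visit view can be derived later. That is true and makes the remedy cheap. But Section 9.5.1 lists the AE tables explicitly, and carrying them out as written produces the imbalance.

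Third, not every abnormal value becomes an AE. Section 8.1.1 applies a clinical filter, Section 8.4.1 has a fluctuating event recorded once, and Section 9.2 counts only events that are new or worse after randomization. These lower p and link successive panels. The filter does not equalise the arms: in the independent model the ratio rises as p falls.

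Some stronger readings are tempting, and the documents do not support them:
- **A roughly threefold inflation is established.** It is not. It rests on an assumed p and on independence, and it disappears for long-lasting abnormalities.
- **Lipid AEs suffer the same 12-to-3 imbalance.** Table 1 shows 5 versus 3. Section 6.5 can be read as lipids and urinalysis at every visit under sirolimus. That conflicts with Table 1 and should be reconciled; only on that reading would the imbalance be near 12 to 3.
- **The extra visits and the V3 EEG distort AE rates broadly.** AE query visits after screening are 13 versus 10. Under Section 1.3.1 standard care brings both arms clinical review and EEG every 4-6 weeks in year one and every 8-12 weeks in year two, and Sections 6 and 6.8 bring those data into the eCRF. This part is minor.
- **The plan lumps all events together and would attribute the excess to sirolimus.** The tables are split by system organ class, preferred term and severity. No between-arm AE test is planned, and relatedness is the investigator's judgement.

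**Conclusion.** The point holds for laboratory AEs from haematology and chemistry. Scheduled looks are up to 12 (or 10) versus at most 3, and the crude tables make no allowance for this. For any abnormality that can resolve between control visits, the tables will show more under sirolimus with no drug effect at all. The direction follows from the schedule and the AE definition; the size does not. About 22% versus 6% up to 72% versus 27% applies to an assumed 2% to 10% independent risk per panel at 12 versus 3. The effect is smaller at 10 versus 3 and for lipids, with a ratio of about 1.4 at 180 days' duration and 1.0 at 365 days. A real drug effect may exist as well, and the crude tables could not separate the two. The primary analysis is untouched and the AE tables are descriptive, so this concerns how the safety comparison is read. It should be corrected in the analysis section and gives no reason to change the visits.

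**What to change.** Keep the all-visit AE tables as descriptive and add to Section 9.5.1:
- A supplementary table by arm of AEs arising from laboratory investigations, restricted to those found at V6, V8 and V12 and shown apart from clinically detected AEs. Identify them by AE dates against the visit date, or by a simple eCRF flag for how the event was detected. An event still open at a common visit should count there. Otherwise an abnormality first seen at a sirolimus-only visit and still present at V6 would be dropped, and the comparison would tilt the other way.
- The number of laboratory assessments actually done per arm, since controls may decline them.
- A sentence that between-arm statements on laboratory AEs rest on this table and the by-visit laboratory tables.

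**Cost:** one or two tables and at most one eCRF field, with no extra visit or blood sample. **Downside:** the restricted table leaves out the sirolimus-only visits, including titration. Those events remain in the all-visit tables.
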